#### Neurocognitive measures

Despite the role of the prefrontal cortex in higher cognitive processes [44], the effect of HF-rTMS over the rDLPFC on neurocognitive measures in alcohol dependent individuals is poorly investigated (see also [22]). Therefore the effect of active HF-rTMS compared with sham HF-rTMS on several neurocognitive tasks will be assessed before the first, after the fifth and tenth HF-rTMS session. Neurocognitive tasks will focus on cognitive control and other relevant processes such as approach behavior and working memory. Participants will be situated in front of a finger operated touch screen tablet (Hewlett-Packard; Windows 8.1) on which the tasks will be conducted.Go/ No-go Task (GNGT): This task (adapted from [45]) measures the ability to refrain from action initiation [46]. Participants see a number (‘1’, ‘2’, ‘3’, ‘4’, ‘5’, ‘6’, ‘7’, ‘8’, ‘9’) projected on a screen in front of them. They are instructed to press the spacebar with their right hand as soon as they see a number, but not if it is the number ‘3’ (=no-go trial) (Fig. 2a). The outcome measure will be the number of commission errors, i.e. a response to a no-go trial, reflecting action impulsivity. The higher the number of commission errors, the more impulsive an individual is.Approach Avoidance Task (AAT): This task (adapted from [47]) measures the bias towards approaching alcoholic beverages. During this task pictures from a validated dataset [48] of alcoholic beverages, sodas and neutral objects (for example scissors) are presented on a screen in front of the participant. The pictures are rotated 3° towards the left or right, indicating whether a participant has to pull or push a picture using a joystick (Fig. 2b). When a picture is pulled or pushed the size of the picture increases or decreases respectively. The bias score per stimulus category [alcohol/ soda/ neutral] will be calculated by subtracting the median reaction time of the approach (pull) trials from the median reaction time of the avoid (push) trials. When the result of this subtraction is positive, this indicates a relative faster approach compared to avoid, i.e. an approach bias. When the result of the subtraction is negative this indicates a relatively faster avoid compared to approach, i.e. avoid- bias.Delay Discounting Task (DDT): This task (based on [49]) measures the extent of impulsive decision making. Participants are presented with a choice between an immediate (lower) and a delayed (higher) hypothetical monetary reward (Fig. 2c). The value of the immediate reward varies across the trials in one block, and depends on the responses that are made [49]. The outcome measure will be the area under the discounting curve (AUC), reflecting the degree of discounting by delay [50]. Impulsive choice behavior is indicated by a smaller AUC.Spatial Working Memory Task (SWMT): This task is part of the Cambridge Neuropsychological Test Automated Battery (CANTAB) test battery, and measures the ability of a subject to remember spatial information and manipulate this using working memory. During this task participants are presented with a number of colored squares (or boxes for the participant) shown on a screen. The participant is instructed to find a blue token hidden in each box, and use this token to fill up the black empty space on the right side of the screen (Fig. 2d). In order to open a box, and see whether there is a hidden token inside, the participant needs to touch the box on the screen. If no token is found the participant must continue its search until a token is found. When there is a blue token inside, the participant must now touch the black empty space to fill up this space with the token. Now the participant has to begin a new search. The next token will only be hidden in a box that so far has been empty. This procedure is repeated until all tokens are found and the entire empty space is filled with tokens. The task starts with three boxes, and this will increase to four, six and eight boxes. Touching a box where the token had already been found is considered an error. The outcome measure will be the number of errors a subject makes and reflects working memory capacity. The more errors a subject makes, the lower the working memory capacity.Stop Signal Task (SST): This task (part of the CANTAB test battery) measures the ability of an individual to inhibit an ongoing action [46]. Participants are presented with a white ring on a black screen. In the ring a white arrow pointing either to the left or to the right appears. The participant needs to press the left button if the arrow points to the left and the right button when the arrow points to the right as fast as possible (go trial). During some trials the participant hears an auditory signal (beep), after the arrow appears, which indicates they have to stop their response and not press the button (stop trial) (Fig. 2e). The outcome measure will be the amount of successful stops and reflects the capability of stopping an initiated response. The lower the number of successful stops, the more impulsive an individual is.Intra-dimensional/ Extra- dimensional Set Shift (IDED): This task (part from the CANTAB test battery) tests rule acquisition and reversal learning. Two stimuli are presented on a screen from which the participant has to choose one by pressing on the screen. These stimuli are made up of two artificial dimensions: color-filled shapes and/or white lines. The stimuli presented can be either simple (just one of the two dimensions) or compound (stimuli contain both the dimensions). The task contains 9 blocks increasing in difficulty (Fig. 2f). After pressing the stimulus on the screen the computer gives feedback on whether this was the correct stimulus. In this way participants can learn the task rules. After six correct responses (learning criterion) the program changes the rule, and thereby the participant reaches the next block. If the participant does not reach the learning criterion the test terminates after 50 trials. The outcome measures will be the number of trials needed to reach the next stage (indicating the rule learning capacity), and the number of errors made after a rule change (indicating the capacity of reversal learning) [51]. Higher numbers indicate lower rule learning and reversal learning capacity.

**Fig. 2 Fig2:**
[figure not shown]
Graphical representation of the neurocognitive measures. **a** Go/ No-go Task (GNGT), **b** Approach Avoidance Task (AAT), **c** Delay discounting task (DDT), **d** Stop signal task (SST), **e** Spatial Working Memory Task (SWMT), **f** Intra-dimensional/ Extra- dimensional Set Shift (IDED). Fig. E-F are adapted from the CANTAB instruction manual

#### Neuroimaging measures

Because the effect of HF- rTMS over the rDLPFC of alcohol dependent individuals on brain functioning is poorly investigated [22], several cognitive tasks will be conducted while functional Magnetic Resonance Imaging (fMRI) is performed. Furthermore, as a control measure, arterial spin labelling (ASL) MRI will be performed in order to investigate changes in cerebral blood flow [52]. MRI scanning will be performed on a 3.0-Tesla Intera full-body scanner (Philips Medical Systems, Best, the Netherlands) with a 32 channel sense head coil located near the Academic Medical Centre in Amsterdam.Cue reactivity task: This task (adapted from [53]) measures the neural response during presentation of alcohol and neutral pictures. The task consists of ten blocks, subdivided into five alcohol and five neutral blocks, presented alternatingly. Each blocks contains seven trials which each show one picture. Of these seven trials, six have a relevant content, and one is a target, namely an animal. The participants are instructed to thoroughly look at all the pictures, and press the right button when they see an animal. Before and after the task the participant will be asked to rate “how much do you feel like drinking alcohol right now?” on a 10 point scale in which 1 indicates “not at all” and 10 indicates “very much” [53]. We will compare neuronal activity during watching alcohol pictures with neuronal activity during watching neutral pictures.Stroop task: This task (adapted from [54]) measures the neural response during watching two types of stimuli, congruent or incongruent. All trials contain one of the following words in Dutch: “red”, “blue”, “yellow”, “green”. In congruent trials the color of the word is the same as the content of the word, while during incongruent trials the color of the word is different from the content of the word. Participants are instructed to indicate the color of the word by pressing on the representative button [54]. We will compare neuronal activity during the incongruent trials with the congruent trials.Monetary Incentive Delay Task (MIDT): This task adapted from [55, 56] measures the neural response during the anticipation of a reward. Participants are presented with cues (blue triangle or blue circle) that indicate whether they could earn €0.01 or €0.50. The cue is followed by a target (green star). The participant is instructed to press the right button as soon as possible when they see the target. If the participant is fast enough, he/she earns the amount of money. This is communicated to the participant through a feedback screen in which both the amount of earned money as well as the total amount of money is presented. We will compare the neuronal response during the anticipation of the high reward with activity during the anticipation of the low reward.Resting state task: During this scan (adopted from [57]) the neuronal activity of the resting state network will be measured. Participants are presented with a black screen and instructed to close their eyes, not think of something in particular, just let their minds wander and try not to fall asleep [23]. Functional connectivity of the rDLPFC will be determined.

### Statistical analyses

#### Power analysis

The current study is the first to investigate the effect of multiple HF-rTMS sessions on abstinence rates measured six months after the last stimulation session. To the best of our knowledge no studies thus far have investigated the effect of rTMS on abstinence after a longer - clinically more relevant - period of time. Therefore no effect size is known or can be calculated, which makes it impossible to perform a scientifically correct power analysis. However, to estimate how many participants we would need, we based our population estimate on a previous study with a similar design [20], which used craving as the outcome of interest. Although our secondary outcome measure is craving, we hypothesized that we should at least include a similar number of participants (30 participants in the active stimulation group) as [20]. Given a drop-out percentage of 10%, and an estimated lower effect on behavioral measures compared to craving, the current study will include 38–40 alcohol dependent individuals per group, resulting in a total of approximately 80 participants.

##### Neuroimaging study part

For the neuroimaging sub-study no information about the effect-size is available. However, studies of the statistical properties of one large fMRI cohort found that the sensitivity and reproducibility of group analyses reaches a plateau at *N* = 27 [58]. With this sample size, the proportion of correct classification of truly active and inactive voxels corrected for chance is k > 0.75. In line, this sample size is also similar to the sample size that is typically used for neuroimaging studies that compare psychiatric patients with healthy controls (*N* = 20–30) [59]. Therefore 28 participants of each group will be included in the neuroimaging study part.

#### Descriptive statistics

Descriptive analyses will be performed in order to see whether randomization resulted in two research groups with a similar distribution of demographic factors. Appropriate parametric and non-parametric statistical tests will be used to analyze descriptive statistics, and if required, multiple comparison corrections will be performed.

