## Methods/ design

### Study design

The effectiveness of the HF-rTMS add-on treatment will be tested in a parallel, single center, single blind trial in abstinent alcohol dependent subjects, randomized (1:1) to either treatment as usual (TAU) plus 10 sessions of active HF-rTMS or TAU plus 10 sessions of sham HF-rTMS. A subset of the participants will undergo a magnetic resonance imaging (MRI) scan prior to the first and after the last stimulation session in order to investigate the effects of HF-rTMS on brain functioning (referred to as neuroimaging study part).

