### Procedure and data collection

#### Inclusion procedure

The participants will start their TAU at a clinical or day detoxification unit where they stay for 7–10 days, and continue their treatment during an intensive 3–5 days treatment of at least three weeks. During the beginning of their treatment participants are informed of the study by the researcher. Individuals who are interested in participation are invited for an appointment to provide them with more information. If they are interested, informed consent is signed and the participant is screened for inclusion and exclusion criteria. If a patient meets all inclusion criteria and none of the exclusion criteria he/she will be included in the study by the researcher. After inclusion the patients can indicate whether they also want to participate in the neuroimaging study part. In that case a subsequent MR screening is performed. In order to assure concealed randomization, participants are assigned to the sham or active stimulation group after inclusion, based on the stratification factors anti-craving medication (yes / no) and age (20–40 / 41–65) using variable block sizes (4, 6 and 8) of the randomisation module implemented in the data management system Castor EDC (Castor Electronic Data Capture, Ciwit BV, Amsterdam, The Netherlands, 2016). After randomization participants start with the research procedure described below.

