#### Primary outcome measure

Data of the primary outcome measure will be analyzed in accordance with the intention-to-treat principle. Missing data of subjects that are randomized and received at least one stimulation session will be imputed in order to achieve complete datasets. Subsequently an appropriate test for comparing two groups will be used depending on the distribution of the outcome measure. Additionally, data of the primary outcome measure will be analyzed with only treatment completers (according to the per protocol analysis), again using an appropriate test depending on the distribution of the outcome measure.

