#### Secondary outcome measures

An appropriate test for comparison of two groups will be used depending on the distribution of the outcome measures ‘days until first relapse’ and ‘total alcohol consumption’.

Multilevel models (capable of handling missing data points) with predictors time, treatment and time X treatment interaction will be used to test for the effect of the HF-rTMS add-on treatment on craving. The following time points will be included: post HF-rTMS, 3 months follow up and 6 months follow up.

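### Baseline significance tests cannot show that randomisation gave similar groups, and the unadjusted primary comparison gives up precision

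*Protocol article*

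**What the plan says.** Under Descriptive statistics, the protocol article gives the purpose of the baseline comparison: "Descriptive analyses will be performed in order to see whether randomization resulted in two research groups with a similar distribution of demographic factors". It then names the method: "Appropriate parametric and non-parametric statistical tests will be used to analyze descriptive statistics, and if required, multiple comparison corrections will be performed". It gives no significance level, number of tests, correction method or margin, and it does not say what follows from a significant or non-significant result.

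For the primary outcome, abstinent days in the 180 days after the last session, the analysis section says: "Subsequently an appropriate test for comparing two groups will be used depending on the distribution of the outcome measure". No covariate is named. Days to first relapse and total consumption are handled in the same way. For craving, the plan is "Multilevel models (capable of handling missing data points) with predictors time, treatment and time X treatment interaction", with time points that start after treatment.

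Randomisation is stratified by anti-craving medication and by two age bands (Inclusion procedure). Neither factor appears in the stated primary analysis. Table 1 shows that alcohol use history and the AUDIT are collected on test day 1.

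**The concern.** Three things do not fit together.

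- **The test answers a question already settled.** With concealed randomisation, any baseline difference arose by chance. A p-value tests exactly that, so it cannot say whether the arms are close enough for a fair reading of the result. No margin is set, so a non-significant result is not evidence of similarity.
- **The correction works against the stated purpose.** A stricter threshold makes a real imbalance in the sample easier to overlook.
- **Nothing downstream uses prognostic information.** The stated comparison takes no account of baseline variables, whether or not a test flags them.

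At stake is how one small trial is read. A report could say that the groups were similar on the strength of p-values while a visible imbalance in a prognostic variable sits in the estimated difference in abstinent days. Precision that the trial has already paid for, through stratification and the baseline interviews, would also go unused.

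**Working it through.** **Inputs from the protocol article.** Allocation is 1:1 (Study design), and "the current study will include 38–40 alcohol dependent individuals per group, resulting in a total of approximately 80 participants" (Power analysis). I use 40 per arm.

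**Assumptions, not in the document.** Two-sided alpha 0.05, Bonferroni over k tests, a roughly normal baseline variable, and a baseline-outcome correlation r of 0.3 or 0.5. The Fig. 1 caption lists nine sample characteristics, so k up to about 10 is plausible, but the protocol gives no count. It also states no threshold for these tests, so there is no figure to reproduce.

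**Step 1: what goes unflagged.** In SD units, the standard error of a difference in means is sqrt(2/40) = 0.2236. The largest observed difference that stays non-significant is the critical t (78 df) times 0.2236.

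| k | alpha per test | critical t | largest unflagged difference (SD) |
|---|---|---|---|
| 1 | 0.05 | 1.991 | 0.445 |
| 2 | 0.025 | 2.286 | 0.511 |
| 5 | 0.01 | 2.640 | 0.590 |
| 10 | 0.005 | 2.889 | 0.646 |

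**Step 2: an observed 0.5-SD imbalance.** t = 0.5/0.2236 = 2.24, p = 0.028 (at 38 per arm, t = 2.18, p = 0.032). It is flagged without correction and missed with Bonferroni over as few as two tests.

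**Step 3: effect on the realised estimate.** An imbalance of d SD shifts the unadjusted difference by r × d outcome SDs. For d = 0.44 this is 0.3 × 0.44 = 0.13 SD or 0.5 × 0.44 = 0.22 SD. The second is about as large as the standard error of the comparison (0.22 SD).

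With no treatment effect and b = r × d/0.2236, the chance of p < 0.05 given that imbalance is approximately P(Z > (1.96 − b)/sqrt(1 − r²)) + P(Z < (−1.96 − b)/sqrt(1 − r²)).

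| d (SD) | r = 0.3 | r = 0.5 |
|---|---|---|
| 0.44 | 8% | 13% |
| 0.60 | 11% | 24% |

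**Step 4: average over randomisations.** In simulated null trials of 40 per arm, the unadjusted test rejects about 5% of the time overall. Among trials whose baseline test is non-significant, it rejects between 4% and 5% of the time.

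**Step 5: precision.** For a continuous outcome, adjusting for a variable with correlation r multiplies the residual variance by 1 − r². This is 1 − 0.09 = 0.91 at r = 0.3 and 1 − 0.25 = 0.75 at r = 0.5, a reduction of 9% or 25%. For a bounded count these figures are only a guide.

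**The case against.** The strongest reply is that no error rate is broken. The unadjusted randomised comparison is valid, and Step 4 shows that calling the groups similar does not raise the average false-positive rate above 5%. This stands. The higher figures in Step 3 hold only given an imbalance of that size, and 0.60 SD (p = 0.009) would itself be flagged without correction and with Bonferroni over 5. What remains is lost precision and the reading of the one trial that is run.

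A reader might infer that a 0.5-SD imbalance would usually be declared similar. The document does not support that. Without correction an observed 0.5 SD is flagged. A true 0.5-SD population difference would be missed about 40% of the time, and randomisation rules out such a difference anyway. The stronger statement needs correction over several tests, which the protocol makes conditional and does not specify.

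A reader might also infer a rule that non-significant variables go unadjusted. None is stated: the baseline tests are linked to no later step. This is a condensed article, and covariate detail may sit in an analysis plan that is not shown, so the lack of a covariate list alone would not be a point. The point rests on what the article commits to: significance tests as the means of assessing similarity, and a two-group test as the primary comparison.

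Finally, stratification protects the two age bands and anti-craving medication. It does not protect drinking history, AUDIT or education.

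**Conclusion.** The point holds in limited form. The plan uses a tool that cannot show similarity, and the optional correction widens what passes unnoticed from 0.445 SD to 0.51 SD (2 tests) or 0.65 SD (10 tests) at 40 per arm. These limits rest on assumed two-sided alpha 0.05 and Bonferroni.

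The stated primary comparison is valid at 5% on average. It forgoes precision, by 9% to 25% of residual variance if the correlation is 0.3 to 0.5, and it leaves chance imbalance in the realised estimate. Neither a general inflation of false positives nor a planned misdeclaration of similarity follows from the document. The change is worth making because it is cheap.

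**What to change.** - Delete the baseline significance tests and their multiplicity correction. Report each baseline characteristic by arm with its standardised difference, and make no statement of similarity based on p-values.
- Prespecify the primary comparison of abstinent days adjusted for age group, anti-craving medication and one prognostic variable already collected on test day 1, such as alcohol use history or baseline AUDIT. Choose that variable on prognosis before unblinded data are seen, and keep it whatever the observed balance.
- Name a model suited to a count bounded at 0 and 180, for example a proportional-odds or beta-binomial model. A simple rank test does not take covariates, so this changes the analysis method as well as the wording.

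The cost is three degrees of freedom if each covariate takes one, and a regression model in place of a simple two-group test. No new data or participants are needed.

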#### Primary outcome measure

Data of the primary outcome measure will be analyzed in accordance with the intention-to-treat principle. Missing data of subjects that are randomized and received at least one stimulation session will be imputed in order to achieve complete datasets. Subsequently an appropriate test for comparing two groups will be used depending on the distribution of the outcome measure. Additionally, data of the primary outcome measure will be analyzed with only treatment completers (according to the per protocol analysis), again using an appropriate test depending on the distribution of the outcome measure.

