#### Primary outcome measure

The primary outcome of the study will be the abstinence rate after the add-on HF-rTMS treatment (in line with the guidelines of the European Medicines Agency [31]). This will be defined as the number of abstinent days in the 180 days after the last stimulation session measured using the Time Line Follow Back (TLFB) [32] at six months follow up.

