#### Secondary outcome measures

The secondary outcome measures of the study will be described below.Total alcohol consumption after the add-on HF-rTMS treatment. This amount (g) of alcohol will be calculated using the TLFB at three months and six months follow-up.Days until the first relapse after the add-on HF-rTMS treatment, wherein relapse is defined as a heavy drinking day. This holds more than 60 g alcohol per day for men and more than 40 g alcohol per day for women [31, 33]. This measure will be assessed using the TLFB at three months follow up and six months follow-up. Individuals who do not relapse will receive the highest score of 90 days.Change in craving levels after the add-on HF-rTMS treatment will be measured using the Alcohol Urge Questionnaire (AUQ) [34] assessed after the last session of the add-on HF-rTMS treatment, at three and six months follow-up.

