## Discussion

This paper presents a single blind randomized clinical trial protocol investigating whether 10 sessions of active HF-rTMS compared with 10 sessions of sham HF-rTMS improve the treatment outcomes of alcohol dependence. The aim of this study is to increase abstinence rates, decrease craving, and improve neurocognitive and brain functioning measures relevant for alcohol dependence treatment.

The main challenge of this study will be completion of the entire follow-up procedure. Participants will be called three, six and twelve months after finishing the last stimulation session to assess the number of abstinent days. Within the population of alcohol dependent individuals, chances are high that participants will get lost at follow-up [62]. There is a risk that we may not get the primary outcome measure for all participants, because it is uncertain whether we can reach all participants at six months follow-up. However, our research group is experienced with a six months follow-up and no main problems have been reported in reaching participants.

The first strength of this study is that it investigates the effect of *multiple* HF-rTMS session. The second strength of this study is that it takes into account several aspects that are important in the treatment of alcohol dependence. So far studies mainly looked at the effect of HF-rTMS on self-reported craving, although the most relevant clinical question is whether HF-rTMS has an effect on abstinence [22]. This study will perform follow-up measurements to assess the number of abstinent days in the six months after the last neurostimulation session. Furthermore this study will elucidate the underlying mechanism by which rTMS may induce its effects in alcohol dependent individuals by investigating several neurocognitive as well as neuroimaging measures [22].

The limitation of this study is that the trial is not double blind controlled. However, a double blind controlled rTMS study with a sham condition similar to this study is impossible because the researcher needs to tilt the coil 90° relative to the skull [23]. Because this study only uses participants self-report measures and the researcher does not score any clinical effects, the outcome measures are not affected by the knowledge of the researcher, and a double blind paradigm is not necessary.

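### The intention-to-treat primary analysis leaves randomised patients who never start stimulation without a defined outcome, and gives the three-month drinking interview no role in the primary count

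*Protocol article*

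**What the plan says.** Under Statistical analyses, Primary outcome measure, the protocol article names the principle: "Data of the primary outcome measure will be analyzed in accordance with the intention-to-treat principle". The next sentence sets the rule for incomplete data: "Missing data of subjects that are randomized and received at least one stimulation session will be imputed in order to achieve complete datasets". A separate analysis of treatment completers is planned alongside.

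Under Outcomes and instruments, Primary outcome measure, the endpoint is "the number of abstinent days in the 180 days after the last stimulation session measured using the Time Line Follow Back (TLFB"). The interview that supplies it is given in the singular: "measured using the Time Line Follow Back (TLFB) [32] at six months follow up".

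For total alcohol consumption, under Secondary outcome measures, the source is wider: "This amount (g) of alcohol will be calculated using the TLFB at three months and six months follow-up". Days until first relapse also draws on both interviews. Table 1 shows the TLFB at three, six and twelve months, and the Discussion says: "Participants will be called three, six and twelve months after finishing the last stimulation session to assess the number of abstinent days".

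On timing, the Inclusion procedure places allocation after screening and inclusion, and then says: "After randomization participants start with the research procedure described below". On follow-up, the Discussion concedes: "There is a risk that we may not get the primary outcome measure for all participants".

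**The concern.** There are two separate weaknesses in how the primary outcome is fixed.

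First, intention-to-treat means that everyone randomised counts in the arm to which they were allocated. A condition of at least one session describes a different set, usually called modified intention-to-treat. The time origin makes this more than a matter of wording: a patient with no session has no last session, so the 180 days cannot be placed. If patients who never start differ from the others, and do so unequally between arms, the primary comparison is no longer protected by randomisation.

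Second, the article names completing follow-up as the trial's chief difficulty, yet defines the primary count from the six-month interview alone. A patient reached at three months but not at six has about half of the 180 days already recorded. The definition does not say that those days count.

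**Working it through.** The plan gives no figure on this point to reproduce. It has no rate of never-starting, no expected number of abstinent days and no standard deviation. Steps 1, 2 and 4 are readings of the text; steps 3 and 5 give scale only, on stated assumptions.

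**Step 1. Can a patient be randomised and never stimulated?** Yes. Allocation comes before the research procedure (Inclusion procedure). For the imaging subset, that procedure includes a scan during the week leading up to session 1 (Procedure and data collection, Neuroimaging study part). The subset is 28 per group (Power analysis, Neuroimaging study part), so 2 × 28 = 56 of about 80 patients have an interval built in between allocation and first stimulation.

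**Step 2. What does the stated rule give each type of patient?**

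| Randomised patient | Start of the 180 days | Missing value imputed? |
|---|---|---|
| Completes 10 sessions | session 10 | yes |
| Stops early | last session received | yes |
| Receives no session | none exists | no |

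The third row has no observed value and no imputed value. The text does not say that these patients are excluded, but nothing is left to analyse.

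**Step 3. Scale of the omission.** Let *k* of 40 patients in one arm be omitted, with *g* fewer abstinent days on average than the other patients, whose mean is *m*.

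- Mean over all randomised = [(40 − *k*)·*m* + *k*·(*m* − *g*)] / 40 = *m* − *k·g*/40.
- Mean as analysed = *m*, so the arm shifts by *k·g*/40.

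The only loss figure in the document is the 10% drop-out in the Power analysis: 0.10 × 40 = 4 per arm. It is not split by timing, so *k* = 4 puts all of it before session 1. With *g* assumed to be 30 to 120 days:

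- *k* = 1: 0.8 to 3.0 days
- *k* = 2: 1.5 to 6.0 days
- *k* = 4: 3.0 to 12.0 days

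With active = A and sham = S, the shift in the between-arm difference is (*k*_A·*g*_A − *k*_S·*g*_S)/40. It is zero if number and gap are equal in both arms, and its sign depends on which arm has more such patients and on whether they do worse or better.

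**Step 4. Early stoppers.** Sessions run on 10 consecutive workdays (Intervention). Stopping after session 1 moves the origin by 9 workdays, about 11 to 13 calendar days. The window still lasts 180 days, so this effect is small.

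**Step 5. What the three-month interview could contribute.** Assume that it covers about days 1–90 and that abstinent days in the two halves have equal variance σ² and correlation *r*. For the total *T* = *A* + *B*, where *A* and *B* are the first and second halves:

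- Var(*T*) = 2σ²(1 + *r*) and Cov(*A*, *T*) = σ²(1 + *r*).
- Share of Var(*T*) explained by *A* = σ⁴(1 + *r*)² / [σ² · 2σ²(1 + *r*)] = (1 + *r*)/2.

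For *r* = 0.3, 0.5, 0.7 and 0.9 this is 65%, 75%, 85% and 95%.

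**The case against.** The strongest reply is that the text restricts who is imputed, not who is analysed, so exclusion is an inference. That is right as a matter of wording. It does not rescue the rule, because a patient with neither a window nor an imputed value cannot enter the comparison.

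A reader might infer that the three-month data are thrown away, or that anyone missed at six months is imputed for the whole 180 days as if nothing were known. The documents do not say so. Imputation is promised without naming a model. The model may be set out in the analysis plan or full protocol, which are not shown, and it could use the three-month days. The Discussion also says that the calls at all three time points assess abstinent days. What stands is narrower: the definition of the primary outcome gives the three-month TLFB no role, while related secondary outcomes use it.

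A reader might also infer from Table 1, which puts the MINI on test day 1, that patients are removed after allocation when an exclusion diagnosis appears. The Inclusion procedure has all criteria screened before inclusion, and no section describes removal afterwards.

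Finally, a reader might infer a bias in favour of active stimulation because the researcher is not blind. Allocation is concealed, participants are blind, and someone who leaves before session 1 has had no stimulation from which to guess the arm. The documents describe no route to unequal non-starting. The Discussion's defence of single blinding concerns how outcomes are scored and does not address who enters the analysis, but that leaves the direction of any bias unknown.

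**Conclusion.** The point holds in two limited parts. The intention-to-treat label does not fit the one-session condition, and with the window tied to the last session, never-starters have no defined outcome. Separately, the primary count is tied to the six-month TLFB alone although the three-month TLFB is collected.

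Neither the size nor the direction of any bias follows from the documents. The shifts in one arm's mean (0.8 to 12.0 days) rest on assumed numbers and gaps, and the upper end needs the entire drop-out allowance of one arm to fall before session 1. The 65% to 95% explained by the first half rests on an assumed correlation and equal variances. It shows what the three-month interview could supply, not what the present plan forgoes, because the imputation model is not shown. This should be corrected, since the remedy is cheap, but it is not evidence that the trial's result would be wrong.

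**What to change.** - **Analysis set.** Analyse all randomised patients in the arm to which they were allocated, with no condition on sessions received. The planned completer analysis still gives a treated-only estimate.
- **Time origin.** Start the 180 days on a date that every randomised patient has, such as the scheduled date of session 10, and time the three- and six-month calls from it.
- **Outcome.** Build the count from the three-month TLFB (about days 1–90) and the six-month TLFB (about days 91–180). The article does not state how far back each interview reaches, so record this, and say which interview takes precedence where both cover a day.
- **Imputation.** Impute only days that neither interview covers, with the three-month abstinent days among the predictors.

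The cost is a change of wording and follow-up calls to the few patients who never start. The estimated effect may become slightly smaller, because untreated patients are counted in their allocated arm.

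At a minimum, if the one-session condition is kept, call the set modified intention-to-treat, justify it, and report by arm how many randomised patients received no session.
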